## Abstract

**Background:**

Mobile phone ownership and access have increased rapidly across low- and middle-income countries (LMICs) within the last decade. Concomitantly, LMICs are experiencing demographic and epidemiologic transitions, where non-communicable diseases (NCDs) are increasingly becoming leading causes of morbidity and mortality. Mobile phone surveys could aid data collection for prevention and control of these NCDs but limited evidence of their feasibility exists.

**Objective:**

The objective of this paper is to describe a series of sub-studies aimed at optimizing the delivery of interactive voice response (IVR) and computer-assisted telephone interviews (CATI) for NCD risk factor data collection in LMICs. These sub-studies are designed to assess the effect of factors such as airtime incentive timing, amount, and structure, survey introduction characteristics, different sampling frames, and survey modality on key survey metrics, such as survey response, completion, and attrition rates.

**Methods:**

In a series of sub-studies, participants will be randomly assigned to receive different airtime incentive amounts (eg, 10 minutes of airtime versus 20 minutes of airtime), different incentive delivery timings (airtime delivered before survey begins versus delivery upon completion of survey), different survey introductions (informational versus motivational), different narrative voices (male versus female), and different sampling frames (random digit dialing versus mobile network operator-provided numbers) to examine which study arms will yield the highest response and completion rates. Furthermore, response and completion rates and the inter-modal reliability of the IVR and CATI delivery methods will be compared.

**Results:**

Research activities are expected to be completed in Bangladesh, Tanzania, and Uganda in 2017.

**Conclusions:**

This is one of the first studies to examine the feasibility of using IVR and CATI for systematic collection of NCD risk factor information in LMICs. Our findings will inform the future design and implementation of mobile phone surveys in LMICs.

## Introduction

Effective prevention and control of non-communicable diseases (NCDs) centers on surveillance and reduction of exposure to risk factors that give rise to these conditions. Four behavioral, and largely modifiable, risk factors account for the majority of NCDs: unhealthy diet, tobacco use, inadequate physical activity, and excessive use of alcohol [1]. Surveillance provides crucial information on disease burden to guide resource planning and allocation and evaluation of public health interventions and programs [2]. Unfortunately, many low- and middle-income countries (LMICs) face the challenge of implementing effective and systematic ways of tracking NCD risk factors and collecting timely and high-quality data. The rise of mobile phones in LMICs presents an opportunity to use this technology to aid NCD risk factor data collection. Currently, worldwide mobile phone subscriptions have reached 99.7 subscriptions per 100 persons, with 94.1 subscriptions per 100 persons in LMICs [3].

High levels of mobile phone access and ownership afford new opportunities to conduct surveys. As a complement to household surveys, respondents can be interviewed over their personal mobile phones. The most common types of mobile phone surveys (MPSs) are short message service (SMS), computer-assisted telephone interview (CATI), and interactive voice response (IVR). In CATI, an interviewer questions the respondent over the phone. With SMS, brief text messages are used to communicate between devices [4]. In IVR, users interact with a database programmed with questions and a series of pre-recorded answers to the questions, linked to a specific numeric key or numeric response on a touch-tone phone keypad (eg, “Press 1 if you are male, press 3 if you are female”).

The use of MPSs to collect population health estimates in LMICs is in its early stages [5]. Similarly, there is little evidence on the usability and reliability of MPSs and mechanisms to improve survey response, completion and representativeness in LMIC settings. Through a series of 7 sub-studies, this protocol seeks to address the following specific objectives: (1) evaluate the impact of incentive amount, timing, and structure on response, completion, and refusal rates of an IVR-administered NCD risk factor survey; (2) assess the effect of different survey introduction content (eg, informational versus motivational introduction) and modality on response, completion, and refusal rates of an IVR-administered NCD risk factor survey; (3) examine the differences in survey metrics, such as representativeness, completeness, and response rate between different sampling frames of mobile phone numbers; and (4) evaluate the differences in response, completion, and refusal rates between IVR and CATI surveys and establish the inter-modal reliability.

The research studies described in this protocol are part of the NCD research and development arm of the Bloomberg Data for Health Initiative (BD4HI). The BD4HI is an effort led by Bloomberg Philanthropies to improve health by improving the quality and availability of public health data across the globe. The motivation, key goals, partners, and components of this initiative have been described in another paper by our research team [6]. Briefly, the BD4HI NCD research and development agenda includes assessing ways to optimize MPS for NCD risk factor data collection in LMICs.

## Methods

### Formative Phase

Prior to the implementation of the sub-studies, a number of formative activities will be conducted to contextualize the use of MPSs for optimal performance in each country. Briefly, a 3-pronged, standardized approach is used to inform the design and adapt a centrally developed NCD questionnaire for IVR delivery in each country. This includes key informant interviews (KII) with personnel (eg, in government, regulatory agencies, and academic experts) who have in-depth knowledge of relevance to NCDs or the conduct of mobile phone surveys. Additionally, we will conduct focus group discussions (FGDs) to explore community perceptions and willingness to participate in a MPS and identify potential challenges, barriers, and solutions. Finally, user-group testing will be carried out where community members complete an IVR survey in the presence of study staff. These formative activities will be used to create a revised questionnaire containing appropriate local examples, terminologies, and measurements. The country-adapted questionnaire and response options will be used in each of the 7 sub-studies.

### Evaluation Phase

#### Setting and Participants

The research activities will be implemented in Bangladesh, Tanzania, and Uganda. Information on collaborating partners, mobile phone subscription rates [7], mobile network operators (MNOs), and survey languages is summarized in Table 1. The term “subscription” in Table 1, and throughout this protocol, refers to different forms of mobile phone ownership including monthly subscriptions and pre-payment options which are common in LMICs.

**Table 1 table1:** Country partners, survey languages, and mobile phone subscriptions in each country.

Country	Mobile phone subscriptions per 100 people, n	Mobile network operators in country, n	Implementing partner	Languages for mobile phone survey
Bangladesh	83	5	Institute of Epidemiology, Disease Control and Research (IEDCR)	Bangla, English
Tanzania	76	5	Ifakara Health Institute (IHI)	Kiswahili, English
Uganda	50	6	Makerere University School of Public Health (MakSPH)	Luganda, Runyakitara, Luo, English

In each of the 3 countries, participants for the MPS, except for sub-study 6, will be selected through random digit dialing (RDD) [8]. For each country, we will identify all active MNOs and their respective prefixes that lead a 10-digit mobile phone number. Using these unique prefixes, the remaining digits will then be randomly generated via a computer to create a random sample of mobile phone numbers to which the surveys will be delivered (Table 2). Participants that are selected using RDD will be asked to provide consent and their age. Participants who do not indicate their age or report being less than 18 years old will be excluded from the study.

#### Study Design

The 7 sub-studies that evaluate mechanisms to improve survey response and cooperation rates of an IVR-administered NCD risk factor survey or compare differences in survey performance between IVR and CATI surveys will be conducted in the 3 countries. The description of each sub-study and a summary of their activities are provided in Table 3. The outcome for every sub-study will be contact, response, completion and refusal rates, and demographic representativeness. In addition, sub-study 7 will include the inter-modal reliability between IVR and CATI-administered surveys.

**Table 2 table2:** Generating a sample through random digit dialing.

Mobile network operator	Unique prefixes^a^	Examples of RDD^b^ phone numbers^c^
A		
	0772-XXX-XXX	[name], [name]
	0773-XXX-XXX	[name], [name]
	0774-XXX-XXX	[name], [name]
B		
	0791-XXX-XXX	[name], [name]
	0792-XXX-XXX	[name], [name]
C		
	0745-XXX-XXX	[name], [name]
	0746-XXX-XXX	[name], [name]
	0720-XXX-XXX	[name], [name]
	0721-XXX-XXX	[name], [name]

^a^Following the unique prefixes, the remaining digits (“X”) are randomly generated using a computer to produce a 10-digit phone number.

^b^RDD: random digit dialing.

^c^The telephone numbers that appear in this table were randomly generated and any similarity with an actual subscriber’s number is purely coincidental.

**Table 3 table3:** Summary description of the sub-studies.

Sub-study	Name	Study arms	Sampling	Country
1	Incentive amount	No airtime	RDD^a^	Bangladesh, Uganda
		X airtime post-IVR^b^		
		2X airtime post-IVR		
2	Incentive timing	No airtime	RDD	Bangladesh, Uganda
		Approximately 20% airtime pre-IVR; approximately 80% airtime post		
		100% airtime post-IVR		
3	Incentive structure	No airtime	RDD	Bangladesh, Uganda
		Fixed X airtime post-IVR		
		Lottery airtime of at least 5X post-IVR		
4	Introduction phrasing and voice	Male voice, informational introduction	RDD	Bangladesh, Uganda
		Female voice, informational introduction		
		Male voice, motivational introduction		
		Female Voice, motivational introduction		
5	Introduction modality	IVR introduction, IVR survey	RDD	Bangladesh, Tanzania
		CATI^c^ introduction, IVR survey		
6	Sampling frame	IVR survey	MNO^d^-provided numbers	Bangladesh
7	Survey modality	CATI survey first, IVR survey 7 days later	RDD	Bangladesh, Tanzania
		IVR survey first, CATI survey 7 days later		

^a^RDD: random digit dialing.

^b^IVR: interactive voice response.

^c^CATI: computer-assisted telephone interview.

^d^MNO: mobile network operator.

#### Sub-Study 1: Incentive Amount

This sub-study evaluates whether there is a differential effect in completion rates of an IVR-administered survey based on the incentive amount. Participants will be randomized to receive 1 of 3 incentive amounts, in the form of airtime, which will be sent to participants upon completion of the IVR survey. The study arms are (1) no incentive; (2) X US dollar airtime incentive, where X is commensurate with the expected time commitment as a function of daily wages (the exact amount will be guided by FGDs and in consultation with country partners); and (3) 2X airtime incentive transferred after survey completion (where 2X is twice the amount of the incentive in arm 2). This sub-study will be conducted in Bangladesh and Uganda.

#### Sub-Study 2: Incentive Timing

This sub-study examines whether the timing of incentive delivery (either pre-survey or post-survey) has an effect on survey response and completion rates of an IVR-administered survey. Participants will be randomized to 1 of the following 3 study arms: (1) no incentive; (2) an airtime incentive sent before the survey, where 10% to 40% of the total incentive (X) is sent to the respondent’s mobile phone prior to initiation of the survey, and with the remaining 60% to 90% being sent after all questions answered; or (3) a promised incentive where 100% of the incentive amount is sent to the respondent’s mobile phone only after the IVR survey is completed. This sub-study will be conducted in Bangladesh and Uganda.

#### Sub-Study 3: Incentive Structure

This sub-study evaluates whether the incentive structure (a fixed incentive amount or a lottery-based incentive) has an effect on completion rate of an IVR-administered survey. Respondents will be randomized to 1 of the following 3 study arms: (1) no incentive; (2) a fixed airtime incentive delivered after survey completion (where the amount of the incentive is guided by sub-study 1); or (3) a lottery airtime incentive of an amount at least 5 times greater than the amount in the second study arm, where the odds of winning the lottery are 1 to 20 (the lottery incentive will be delivered upon completion of the survey and the precise odds for winning will be guided by formative work conducted in each country). This sub-study will be conducted in Bangladesh and Uganda.

#### Sub-Study 4: Introduction Phrasing and Survey Voice

This sub-study assesses whether the content of the IVR survey’s introduction (motivational versus informational) and the survey’s narrative voice (male versus female) has an effect on contact, response, and/or completion rates. Participants will be randomized to 1 of 4 study arms with varying survey introduction content and voices: (1) male survey narrator with an informational survey introduction; (2) male survey narrator with a motivational survey introduction; (3) female survey narrator with an informational survey introduction; or (4) female survey narrator with a motivational survey introduction. The content of the survey’s motivational and informational introductions will be guided by formative work conducted in each country. Participants in each study arm will receive the same airtime incentive. This sub-study will be conducted in Bangladesh and Uganda.

#### Sub-Study 5: Survey Introduction Modality

This sub-study evaluates the effect of the survey introduction’s modality (human operator versus IVR introduction) on survey completion rates. Participants will be randomized to 1 of 2 arms: (1) a CATI-administered introduction with an IVR survey or (2) a full IVR survey. In the first arm, a human will call the RDD-generated mobile phone number, read the survey’s introduction, and the operator will answer any questions the participant may have. Respondents that agree to participate will then be sent an IVR survey. In the second arm, participants will not receive this human introduction. Participants in each study arm will receive the same airtime incentive. This sub-study will be conducted in Bangladesh and Tanzania.

#### Sub-Study 6: Sampling Frame

This sub-study examines whether the source of the mobile phone numbers has a differential effect on IVR survey response and completion rates. The previous sub-studies and sub-Study 7 rely on an RDD sampling frame. In this sub-study, we will obtain a de-identified list of mobile phone numbers from a MNO where participants have consented to be contacted for additional studies. This sub-study will be conducted in Bangladesh.

#### Sub-Study 7: Survey Modality

This sub-study evaluates the effect of the survey modality (IVR versus CATI) on the survey’s response and completion rates and assesses the inter-modal reliability. Participants will be randomized to 1 of 2 arms: (1) IVR then CATI; or (2) CATI then IVR. Participants in the first study arm will receive an IVR survey first, followed by a CATI survey 7 days later (Figure 1). Participants in the second study arm will receive a CATI survey first followed by an IVR survey 7 days later. At initial enrollment, it will be clearly explained to participants that they are being enrolled in a study where they will be contacted twice. The questionnaires used in both study arms will be the same. This crossover design will allow for an assessment of response consistency, adjusted for the risk of “priming” after exposure to the prior modality. This is the only sub-study that will require participants to answer the NCD survey twice. The amount, timing, and structure of incentive will be guided by the first 3 sub-studies where the incentive that yielded the highest response and completion rates will be provided to all participants in sub-study 7. This sub-study will be conducted in Bangladesh and Tanzania.

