### Proposed Sample Sizes

Assuming a baseline survey completion percentage of 30%, in order to detect an absolute 10% difference in survey completion between two study arms at an alpha of .05 and power of 80%, it is calculated that 376 individuals who have completed an IVR survey will be needed in each study arm for each sub-study. With a completion percentage of 30%, we calculated that 1254 participants would be required to consent to the survey per study arm in each country. With 16 study arms total in these 6 sub-studies, 20,064 participants will be enrolled in each country (Table 4). We have not inflated the sample size for multiple comparisons as per the recommendation by Rothman [12]. We chose a 10% difference between study arms as our preliminary analysis indicated that a 1 dollar incentive becomes cost-neutral at this cut-off point.

**Table 4 table4:** Number of participants needed to complete a mobile phone survey per country.

Sub-study	Study arms	Participants who completed survey per study arm, n	Total participants who completed the survey, n
Sub-study 1	3	376	1128
Sub-study 2	3	376	1128
Sub-study 3	3	376	1128
Sub-study 4	4	376	1504
Sub-study 5	2	376	752
Sub-study 6	1	376	376
Sub-study 7^a^	2	405	810
Total			6826

^a^For sub-study 7, we adjust for a 20% loss to follow-up from the first and second mobile phone survey.

For sub-study 7, the sample size is calculated based on the kappa statistic [13]. With assumption of kappa .75, a margin of error of 0.05%, an alpha of .05, and the proportion of positive responses of 0.3, 405 participants who have completed the survey per study arm are needed. Adjusting for a 20% loss to follow-up from the first and second mobile phone survey and a 30% baseline completion percentage, 1688 participants who consented will be enrolled per arm, for a total of 3376 participants across the two arms for each country.

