### Data Management and Analysis

The main outcomes in this study are contact, response, refusal, and completion proportions. Our outcomes are defined based on standard definitions from the 9th edition of the American Association for Public Opinion Research (AAPOR) [14], with some modifications to accommodate our RDD MPS design. Eligible individuals will be defined as persons who confirm that they are at least 18 years old.

Complete interviews (CI) are defined as age-eligible respondents who answer 5 or more modules. Partial interviews (PI) are defined as age-eligible respondents who answer between 2 and 4 modules. Participants who are age-eligible but answer less than 2 modules will be classified as a refusal/break-off (R). Non-contacts (NC) are defined as a confirmed number where respondent never picks up (this classification only applies to sub-studies 6 and 7). The main outcomes will be calculated using the equations in Figure 3.

Outcomes will be tabulated and stratified by both the question number and the question content due to the randomization of NCD topic modules. As a secondary analysis, we will conduct Kaplan-Meier curves to plot survey attrition by time spent on survey. For sub-study 7, test for agreement in survey responses between the survey modalities will be assessed using Cohen kappa. Statistical significance will be determined at an alpha of .05.

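### Sub-study 7: the two-order crossover can show whether agreement differs by order, but it cannot adjust kappa for priming as the protocol says

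*Protocol article*

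**What the plan says.** Under Sub-Study 7: Survey Modality, the protocol article sets up two arms: "Participants will be randomized to 1 of 2 arms: (1) IVR then CATI; or (2) CATI then IVR". The gap is one week in either order; for the second arm the text reads "Participants in the second study arm will receive a CATI survey first followed by an IVR survey 7 days later". On content it says "The questionnaires used in both study arms will be the same". It then states what the design is meant to deliver: "This crossover design will allow for an assessment of response consistency, adjusted for the risk of" priming from the earlier mode.

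Under Data Management and Analysis, agreement gets one clause: "test for agreement in survey responses between the survey modalities will be assessed using Cohen kappa". Nothing there refers to order or priming.

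Under Proposed Sample Sizes, the sub-study is sized on kappa: "With assumption of kappa .75, a margin of error of 0.05%, an alpha of .05, and the proportion of positive responses of 0.3", from which "405 participants who have completed the survey per study arm are needed". Enrolment follows: "Adjusting for a 20% loss to follow-up from the first and second mobile phone survey and a 30% baseline completion percentage", giving 1688 consenting participants per arm and 3376 per country.

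**The concern.** Counterbalancing the order of two modes is a sound way to keep a period effect out of a mean difference between modes. Agreement is a different quantity. It is computed within a person from two answers, and here the second answer always follows exposure to the same questions in the other mode. Swapping the order changes which mode is exposed. It does not produce any pair without exposure.

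The sentence nevertheless tells the reader that consistency is assessed net of priming. The fourth objective in the Introduction includes establishing inter-modal reliability, and kappa is the only agreement measure named for it. A reader who trusts the word *adjusted* will take the reported kappa as cleaned of memory of the first survey, when nothing in the design can clean it.

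**Working it through.** **1. The plan's own figures.** Inputs from Proposed Sample Sizes: kappa k = .75, proportion positive p = .3, alpha .05. The margin is printed as 0.05%; only .05 on the kappa scale gives a sample of this size. The article does not show its formula. The usual large-sample variance for a binary kappa is

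Var = (1 − k)[(1 − k)(1 − 2k) + k(2 − k)/(2p(1 − p))]/N.

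The numerator is .25 × [.25 × (−.5) + .75 × 1.25/.42] = .25 × 2.107 = .5268. Then N = 1.96² × .5268/.05² = 809.5, so 810.

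- 810 is the total over both orders, that is 405 per arm. The stated 405 reproduces on this formula only if the two orders are pooled.
- Half-width with 810: .050. Half-width with one order of 405: 1.96 × √(.5268/405) = .071.
- Half-width for the difference between the two order-specific kappas, both at .75: 1.96 × √(2 × .5268/405) = .10.
- Enrolment: 405/.8/.3 = 1687.5, so 1688 per arm and 3376 in total, as stated.

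**2. What the design can identify.** There are two arms, both mixed-mode, with the same questionnaire and the same interval. No arm repeats the same mode, and no other means of estimating priming is described. Random module order (Questionnaire section) changes the sequence of topics, not the fact of prior exposure. The two order-specific kappas give a contrast, which is informative about a difference in priming between orders. They do not give its level.

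**3. Illustration: priming as repetition.** Assume a share q repeats the first answer, the rest answer with true kappa k₀, and the marginals are equal. Then Po(obs) = q + (1 − q)Po with Pe unchanged, so

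observed kappa = q + (1 − q)k₀, in either order.

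The document gives no value of q; the range is assumed. Solving k₀ = (.75 − q)/(1 − q) for an observed .75:

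| q | k₀ | shift |
|---|---|---|
| .10 | .65/.90 = .72 | .03 |
| .20 | .55/.80 = .69 | .06 |
| .30 | .45/.70 = .64 | .11 |

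The shift equals the .05 margin when .75 − q = .70(1 − q), that is q = .05/.30 = .17.

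**4. Does averaging or contrasting the orders remove it?** Take k₀ = .60.

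- Equal q = .20 in both orders: .20 + .80 × .60 = .68 in each. The contrast is 0 and the pooled value is still .08 too high. A simulation with 405 per arm gave .679 in each order and a difference of about 0.
- Unequal q = .10 and .30: .64 and .72, average .68. The contrast now reveals a difference, but the average keeps the same bias.

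**5. The opposite direction.** Again with k₀ = .60 and p = .3, suppose exposure turns 10% of second-survey *no* answers into *yes*. Before the change the cells are yes-yes .216, discordant .084 each, no-no .616. Afterwards Po = .2244 + .5544 = .7788, the second marginal is .37, Pe = .3 × .37 + .7 × .63 = .552, and kappa = .2268/.448 = .51. With 5% it is .55. So priming can also pull kappa down.

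**6. The unprimed data.** First-survey answers precede any exposure. At 30% completion there are 1688 × .30 = 506 per arm. At 30% prevalence, the 95% interval for an IVR-CATI difference is ±1.96 × √(2 × .3 × .7/506) = ±.056, or about 5.6 points.

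**The case against.** The best defence is that the sentence means something narrower: priming is tied to the mode that came first, and randomised order does allow a check on whether consistency depends on which mode that was. That stands, and it is a real use of the design. But it is a comparison by order, not an adjustment, and the text should say so.

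It can also be said that a condensed article leaves agreement analyses to a fuller document. That is fair for the absence of order-specific kappas or a first-survey comparison, and neither is counted here as an error. It does not rescue the sentence itself, because no analysis of these two arms can recover the level of priming without assumptions from outside the study.

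A reader might go further and infer that kappa will overstate reliability, by the same amount in both orders. The document does not support this. It names a risk of priming without direction, mechanism or symmetry, and steps 4 and 5 show that unequal or downward effects are just as compatible with it. Nor does it say that a kappa near .75 would justify replacing CATI with IVR (.75 is only a planning value), or that second-contact data will be used for the modality effect on response and completion.

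**Conclusion.** The statement is wrong as written: the sub-study 7 crossover can show whether agreement differs by order, but it cannot estimate the level of priming or remove it from kappa. This follows from the two arms alone and needs no assumption about direction or symmetry.

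The size is conditional. Under pure repetition with equal marginals, an observed .75 reflects .72 to .64 for q between .10 and .30, and the shift passes the planned margin only above q of about .17. Under answer-changing priming or real change over 7 days the bias has the other sign. The net direction is therefore open, and describing kappa as an upper-leaning estimate would replace one unsupported claim with another.

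The order contrast is also imprecise at the planned size (about ±.10), so similar kappas in the two orders would be weak evidence even of equal priming, and no evidence that priming is absent.

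**What to change.** 1. Replace the claim of adjustment with two statements: randomised order allows agreement to be compared by order, and the 7-day kappa is not corrected for priming or recall.
2. Report kappa for each order as well as pooled, noting that ±.05 applies to the pooled 810 and about ±.07 to a single order. Correct the printed margin from 0.05% to .05 at the same time.
3. As an unprimed complement, compare first-survey answers between the randomised arms (IVR-first against CATI-first) for each risk factor, adjusted for the demographics already collected. This estimates a prevalence difference by mode, not within-person agreement, so it does not replace kappa. It also conditions on completion, which may differ by mode; the ±5.6 points assumes 30% completion in both arms and ignores any such selection.

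The cost is a reworded sentence and a small amount of analysis on data already planned, with no change to sample size or fieldwork. The downside is a less favourable reading of kappa.
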